### Participants

Children (male and female) who are 0–3 months old at enrolment, reside in the study catchment area and visit the clinic for BCG or Pentavalent-1/Polio-1/PCV-1 vaccination will be approached for screening to participate in the study.

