### Duration

The study will be conducted over 18 months. Immunization data of all enrolled children will be collected at each vaccination visit following his/her enrolment i.e., when s/he visits for Pentavalent-1 vaccine (if enrolled at BCG) at approximately 6 weeks of age, Pentavalent-2 vaccine at approximately 10 weeks of age, Pentavalent-3 vaccine at approximately 14 weeks of age and Measles 1 vaccine at approximately 9 months old. Participation will continue till the Measles 1 vaccine is administered (recommended age is 9 months), or till eleven months have elapsed since child’s enrolment.

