### Data collection methods

At the child’s first visit to the center, the field worker will use an Enrolment Form to note the name and age of the child along with the immunizations received during the visit in addition to basic demographic information.

For the follow-up visits by the caregivers to get the subsequent vaccinations (3–4 visits), our field workers will be based at the participating EPI centers throughout the follow-up period. The field workers will use the unique study IDs to identify study participants when they come for follow-up visits. At each follow-up visit, the field worker will record the vaccine administered, and date of administration for each child enrolled in the study, including verifying data on past immunizations and due vaccines. Therefore, for each study participant, the field workers will collect data 3–4 times during the follow-up period.

After the completion of the follow-up phase, short (15–20 min) phone or in-person interviews will be conducted to collect follow up vaccination data (if missing) and data on experiences of study participants regarding the bracelets. Dropout from the vaccination schedule is also an outcome. We will be able to identify the caregivers who did not show up for the follow up phase, these participants may be contacted through phone or in person visits towards the end of the follow up period. Key data points to be collected will include reasons for drop-outs, whether mothers understood how to use the bracelets, how often mothers said their babies wore the bracelets and why, what mothers liked and disliked about the bracelets and whether mothers would continue using the bracelets as reminders moving forward.

At all points of the study, data will be collected directly from participants using paper-based questionnaires. Immunization data is copied from the child’s government-issued EPI card. All data will be transferred to a secure electronic medium on a daily basis.

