## Discussion

Our expectation is that providing simple to use and easy to understand vaccine reminder bracelets will enable parents to closely keep track and remind themselves of their child’s due vaccines leading to improved coverage and timelines of routine immunizations. Traditionally, to address the global challenge of parents not showing up for vaccination visits [20], low and middle income countries have relied on “Reminder/recall” (RR) interventions including telephone calls, postcards, letters, immunization cards and text messages as a mechanism to remind parents and help in keeping track of children’s vaccination status [21] The standard ‘RR’ protocol utilizes government-issued, paper-based immunization cards. Despite their potential as effective tools for improving vaccination coverage, research into their use has indicated that cards are underutilized and improperly used by caregivers and vaccinators due to lack of literacy among parents and insufficient training of vaccinators in filling out the cards [14]. This results in cards that are illegible, incomplete, or cards that caregivers cannot read or do not value [22]. The most common alternatives to immunization cards that have proven to be effective are phone-based reminders [23, 24]. However, these are resource-intensive at scale and have an uneven impact across the socioeconomic spectrum. A randomized controlled trial in Kenya in 2014 assessing how text-message reminders affected childhood immunization dropout rates saw a 13% reduction in dropouts but also concluded that the intervention had not mitigated the association between a mother’s lack of education and the heightened risk of dropout [25]. Current interventions are, therefore, not optimal solutions in settings with financial and human resource constraints, lack of reliable immunization data on which to base reminders as well as poor coordination between parents and healthcare providers [26].

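### Study contact with non-attenders has two unreconciled timings, and one of them could prompt Measles-1 doses while they still count towards the outcome

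*Protocol article*

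**What the plan says.** The third paragraph of Data collection methods (protocol article) places contact with caregivers at two different times. It first states: "After the completion of the follow-up phase, short (15–20 min) phone or in-person interviews will be conducted to collect follow up vaccination data". It then turns to caregivers who failed to attend and says that "these participants may be contacted through phone or in person visits towards the end of the follow up period". The listed purpose is to gather information, such as reasons for dropping out and experience with the bracelets. The same paragraph names drop-out as an outcome, and Table 1 lists it as an indicator.

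The Duration section sets the outcome window: "Participation will continue till the Measles 1 vaccine is administered (recommended age is 9 months), or till eleven months have elapsed since child’s enrolment". Under Participants, eligible children are those "who are 0–3 months old at enrolment".

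Three other places bear on the point:

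- The end of the Interventions section says that the bracelet is the only difference from standard care and that the comparator arm gets standard care alone.
- Randomization says that neither participants nor the enrolling field staff are blinded.
- The Discussion says of reminder methods: "The most common alternatives to immunization cards that have proven to be effective are phone-based reminders".

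**The concern.** A phone call or home visit that asks why a child has missed vaccinations tells the caregiver that a dose is overdue, whatever its purpose. If it comes before the child's eleven-month cut-off, a Measles-1 dose given in response is recorded as coverage and removes a drop-out. The study would then be adding a reminder of its own, directed only at children who are failing the outcome, in a trial whose intervention is a reminder. A control family reached in this way is no longer receiving standard care alone.

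Analysis cannot repair this. The doses are real and correctly recorded, so neither intention-to-treat analysis nor multiple imputation removes their effect. The article gives no rule for flagging such doses or for making contact alike in all arms. At stake are Measles-1 coverage, which is part of the primary outcome, and the drop-out rate. On-time vaccination is largely settled by then.

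**Working it through.** **1. Is the window still open?** Children enter at 0–3 months and Measles-1 is due at 9 months. Eleven months after enrolment, a child is 0 + 11 = 11 to 3 + 11 = 14 months old. The window therefore closes about 2 to 5 months after the dose is due, and contact late in a child's follow-up can fall inside that interval.

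**2. The plan's own figures (Sample size section).** Two-sided 5%, 80% power, unpooled variance:

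n per arm = (1.960 + 0.842)² × [p₁(1 − p₁) + p₂(1 − p₂)] / (p₂ − p₁)²

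- Pentavalent-3, 60% v 70%: 7.849 × 0.45 / 0.01 = 353.2, so 354. Reproduced.
- Measles-1, 50% v 60%: 7.849 × 0.49 / 0.01 = 384.6, so 385. Reproduced.
- With 20% dropout: 385 / 0.8 = 481.25, so 482 per arm and 1446 in all. Reproduced.

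**3. Equal contact and response in all arms.** Let x be the share of all non-attenders who are vaccinated because of the contact. To count, a child must be contacted, reached, still in the window, and vaccinated as a result. Each rate p becomes p + x(1 − p), so

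difference = (p₂ − p₁)(1 − x).

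Power = Φ( difference / √{[p₁(1 − p₁) + p₂(1 − p₂)] / n} − 1.96 ).

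The documents give no x, so the values below are assumptions. Power is from the unpooled formula, with the pooled version in brackets.

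| x | Control | Bracelet | Difference (points) | Power, 385 per arm | Power, 482 per arm |
|---|---|---|---|---|---|
| 0 | 50% | 60% | 10 | 80.0% (79.8%) | 88.0% (87.8%) |
| 10% | 55% | 64% | 9 | 72.4% (72.1%) | 81.5% (81.3%) |
| 20% | 60% | 68% | 8 | 64.1% (63.8%) | 73.8% (73.6%) |
| 30% | 65% | 72% | 7 | 55.4% (55.2%) | 65.0% (64.8%) |

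Example, x = 10% at 385 per arm: √[(0.2475 + 0.2304) / 385] = 0.0352; 0.09 / 0.0352 = 2.55; 2.55 − 1.96 = 0.59; Φ = 0.72.

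**4. Unequal contact.** Take x = 10% in one arm only.

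- Bracelet arm only: 50% v 60% + 0.1 × 40% = 64%, a difference of 14 points.
- Control arm only: 50% + 0.1 × 50% = 55% v 60%, a difference of 5 points.

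The sign of the bias depends on who is contacted.

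**The case against.** A reader might infer that the trial delivers its own recall to drop-outs and so shrinks the bracelet effect. The documents do not support that as a statement of fact, for these reasons:

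- **Contact is optional and for data collection.** The article says that non-attenders may be contacted and gives no instruction to remind or refer them. A preceding sentence puts interviews after follow-up.
- **The follow-up period may be the study's, not the child's.** The Abstract dates recruitment from 19 July to 10 October 2017, so the eleven-month windows close between 19 June and 10 September 2018. If contact began in the last month, from 10 August 2018, children enrolled before 10 September 2017 would already be past their cut-off. That is 53 of 83 enrolment days, or 64% if enrolment was even (an assumption). Exposure is then much reduced, but about 36% would still be in the window when contact began.
- **Attenuation is not assured.** It needs equal contact and response. Contact is discretionary, enrolling staff know the allocation, and most of the listed questions concern bracelets. Heavier contact in the bracelet arms would enlarge the difference.
- **Potency is unknown.** The favourable remark in the Discussion is about phone reminder programmes, not one late interview. The Background calls the evidence on mHealth mixed and limited.
- **The lower power figures may be pessimistic.** Contact that recovers outcome data moves the analysed number from 385 towards 482 per arm. With x = 10% and 482 per arm, power is still about 81%.

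All of this stands, and it limits the point to a risk of uncertain size and direction. It does not remove it: the text permits contact inside the window, and discretionary contact by staff who may know the allocation is a reason to fix the timing.

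**Conclusion.** The point holds as an unreconciled timing that leaves an avoidable route to bias in Measles-1 coverage and drop-out, and that conflicts with the article's own account of how the arms differ. It does not show that a recall will take place or that the effect will be diluted.

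Given equal contact and response, an assumed x of 10–30% cuts the planned 10-point difference to 9–7 points. Power then falls from 80% to about 72–55% at 385 per arm, or from 88% to about 81–65% at 482. These figures rest on the plan's 50% and 60% rates and on a value of x that the documents do not supply. If contact differs between arms, the bias may go in either direction.

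**What to change.** State one timing in Data collection methods: no study call, visit or interview about missed vaccines is made to any caregiver, in any arm, until that child's eleven-month window has closed. Count only doses dated on or before that day for Measles-1 coverage and drop-out. This limits study contact only; standard care is unchanged.

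If earlier contact has already occurred, log its date and the child's arm. Add a sensitivity analysis that applies one common earlier cut-off, by age or time since enrolment and before contacts began, to all children in all arms. For example, if contact began on 10 August 2018, a cut-off of 10 months after enrolment would precede every contact, since the last child was enrolled on 10 October 2017. Do not simply discard doses given after contact in the contacted children. That would also discard spontaneous late doses and, because only non-attenders are contacted, could remove more of them from the control arm and exaggerate the effect.

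The cost is one sentence in the protocol and a date check in the contact log. Some families would be reached a few weeks later, with slightly more loss of contact or poorer recall.

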### Data management

Data will be entered and stored in computerized databases maintained under password protection. After the completion of data collection, data will be cleaned and de-identified for analysis. To minimize risk from disclosure, the following mechanisms will be instated: Data collected on paper forms at the EPI center will be handed over to the data entry operator on the same day. Data will be transferred to electronic medium on a regular basis while the paper forms will be stored under lock for reference after being scanned and securely stored on an encrypted hard drive. All data collected and obtained through this study will be property of IRD. After the completion of data collection, data will be cleaned and de-identified for analysis and for sharing with PIs at collaborating centers. A secure file transfer server will be used to transmit the data and where possible, transmission of data through email will be avoided.

### Data confidentiality

For all data collected and obtained through this study, the PI and Program Manager responsible for ensuring confidentiality. The respondents’ identity and information collected will be kept confidential through assigning them unique study IDs. Data will be kept in electronic format on password secured computers at IRD for three years after the study has been completed.

### Data monitoring

Regulatory compliance will be monitored by both the Principal Investigator and the management team through random on-site visits to the immunization centers. They will ensure that the research protocols are being adhered to, and administration of consent and questionnaires is being correctly performed. All documentation and record keeping will be done on a daily basis through monitoring sheets recording the number of forms (screening, consent and data collection) administered by each field worker. Where needed, hard copies of all forms will be scanned, and a soft copy will be retained for the record. Refresher training on protocol adherence and record keeping will be delivered by the Program Manager at least twice during the course of the study. There is no formal data monitoring committee for this trial as this is a minimal risk study with a relatively shorter duration.

### Statistical methods

The baseline characteristics of the three groups will be compared by using the Student’s t-test for continuous variables and the chi-square test for categorical variables (using alpha = 0.05 for evaluating statistical significance). We will use intention to treat analysis—that is, all subjects will be analyzed with the assumption that they remained in the treatment group to which they were initially assigned.

$$ \mathsf{Y}=\mathsf{c}+\mathsf{i}.\left(\mathsf{allocation}\ \mathsf{group}\right)+\mathsf{\gamma X}+\mathsf{\varepsilon} $$

Y is the relevant outcome measure (for instance Pentavalent-3 coverage)

C is the constant that gives the value of the outcome for the control group

Allocation group is a categorical variable with 3 levels; “0-Control Group”, “1-Alma Sana Group”, “2-Simple Silicon Group”.

X is the set of possible covariates (gender, mother’s education etc.)

We will use the xi command to create these indicator variables and run the regression/model all in one command on STATA. Logistic regression will be used to determine whether the difference in outcome between the two treatment groups and control group are statistically significant and whether the difference in outcome between the two treatment groups is statistically significant. Multiple imputation will be used to handle missing data. The data will be analyzed in STATA version 15 (StataCorp. 2017. Stata Statistical Software: Release 15. College Station, TX: StataCorp LLC).

### Ethics

This is a minimal risk study, with no possibility of harm to participants beyond the risks associated with standard care. If any adverse event does occur, field staff is instructed to outline any reportable events through an incident report (to be filled either by the staff or study participant) which must be handed over to the Program manager within 24 h of the event occurrence. The report will be filed and the Program manager will review the report and carry out further investigation if necessary, before reporting to Institutional Review Board (IRB) and the donor. Any unanticipated problems and unexpected Serious Adverse Events (SAE) related to study participation will be communicated by study team within 5 business days of the study team becoming aware of the SAE.

To maintain participant privacy, the outlined provisions for data management and monitoring will be adhered to as much as possible. Participants will only be asked questions that are pertinent to the study and wherever possible will be surveyed separately from other caregivers at the study site. For all data collection activities, participants have the right to discontinue the interview at any time or decline to respond to any question.

Ethical approvals for the study were obtained by Institutional Review Boards of Harvard University and Interactive Research and Development.

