### Study site and setting

The study will be conducted in 4 Expanded Program on Immunization (EPI) centers located in Landhi Town, Karachi (list of study sites can be obtained from https://clinicaltrials.gov/ct2/show/study/NCT033107620. Centers will be selected based upon the volume of incoming children. Landhi Town is a peri-urban area in the south of Karachi city, in Pakistan’s Sindh province. Karachi is among the 3 districts in Sindh where polio cases have been detected in 2016; within Karachi, Landhi Town is among the highest risk areas for polio prevalence. Landhi Town has an overall estimated population of 872,000 and an annual birth cohort of 30,514 children. The study introduces an intervention designed primarily for illiterate mothers. Landhi Town provides a feasible setting to test the bracelets since the prospective study participants encompass a lower economic stratum, living on $1.25 per day, have low levels of educational attainment, and live in difficult-to-reach areas.

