### Participant withdrawal

In the event of participant withdrawal from the study due to withdrawing consent, the date and reason for withdrawal will be properly documented. If the participant was in either of the two treatment groups, they will be asked to return the bracelet. Data collected on participants before withdrawal will be retained but not included in the final analysis. Since this is a minimal risk study, we do not expect any discontinuation of interventions in response to harm caused by the bracelets.

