#### Improving adherence

To ensure that participants adhere to the interventions, the study team will ensure at the time of enrolment and at each follow-up visit, that participants are aware of the purpose of the bracelet, how to use it and the importance of making their child wear it at all times. Additionally, at each follow up visit, the participants will be observed for whether their child is wearing the bracelet or not and will be asked if they have any questions regarding the bracelet.

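### The Ethics section rules out any harm beyond standard care although the bracelet is an added exposure, and the stated harm route could under-ascertain bracelet problems

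*Protocol article*

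**What the plan says.** The Ethics section opens by calling this a minimal-risk study "with no possibility of harm to participants beyond the risks associated with standard care". It continues: "If any adverse event does occur, field staff is instructed to outline any reportable events through an incident report". The form is "to be filled either by the staff or study participant" and goes to the program manager, who reviews it before it is passed to the review board and the donor. Unexpected serious events related to participation have a separate reporting timeline.

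Other sections bear on that sentence:

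- **Interventions** (text after Fig. 3): supplying the bracelet is the only difference between the intervention arms and standard care.
- **Improving adherence**: at enrolment and at each follow-up visit, staff make sure families understand "the importance of making their child wear it at all times". At follow-up visits they also note whether the child is wearing it and invite questions about it.
- **Informed consent**: caregivers are told of the risks expected from the study.
- **Participant withdrawal**: the date and reason are documented. "Data collected on participants before withdrawal will be retained but not included in the final analysis". Stopping an intervention because of bracelet harm is not expected.
- **Data collection methods**: an interview after follow-up covers how often the bracelet was worn and why, what mothers liked and disliked, and reasons for drop-out.
- **Outcomes, Table 1**: no safety outcome is listed.

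**The concern.** The claim of zero added risk is made for infants enrolled at 0 to 3 months who are to wear a hole-punched silicone band continuously. Participation lasts until the first measles dose or eleven months after enrolment. Controls have no such exposure. Minimal risk is a defensible description of this; impossibility of harm is not.

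The wording matters more because the dedicated harm route depends on somebody raising a report. Staff already see the child and the bracelet at the follow-up visits, but the article describes no recorded item on problems with it. A family that withdraws consent over such a problem also leaves the analysed set. At stake is what the trial could say about the bracelets as worn objects. The Background calls them safe for babies, and the Discussion envisages their use in any setting. The primary question of coverage and timeliness is not at stake.

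**Working it through.** **1. The statements side by side.** Interventions makes the bracelet the sole difference from standard care, so any harm it causes is by definition harm beyond standard care. Ethics says such harm is impossible. Informed consent speaks of expected risks of the study. Participant withdrawal says only that discontinuation for bracelet harm is not expected, which is a weaker and more reasonable position. The Ethics clause is thus stronger than the article's own related text and cannot be maintained for a worn object.

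**2. Denominator.** The Sample size section gives 385 per arm for Measles-1 (50% versus 60%, two-sided alpha 0.05, power 80%). This reproduces with unpooled variances: (0.5×0.5 + 0.6×0.4) × (1.960 + 0.842)² / 0.10² = 384.6, rounded up to 385. Allowing for 20% dropout, 385 / 0.80 = 481.25, rounded up to 482 per arm, and 3 × 482 = 1446 as stated. The two bracelet arms hold 2 × 482 = 964 infants.

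**3. What zero events could show with complete capture.** The exact one-sided 95% upper bound is 1 − 0.05^(1/n).

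- n = 964: 0.31%
- n = 482 (one bracelet arm): 0.62%
- n = 770 (2 × 385, if only the planned completers contribute): 0.39%

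This is a property of the sample size under any reporting system. It is not itself a defect.

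**4. What incomplete capture would do.** Let s be the share of events that reach a report. The article gives no value for s, so the values below are assumptions. With n = 964, the bound on the true rate after zero reports is 0.31% / s. For an assumed true rate of 0.5%, the chance of at least one report is 1 − (1 − 0.005s)^964.

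| s (assumed) | Upper bound after zero reports | Chance of at least one report at a true rate of 0.5% |
|---|---|---|
| 1 | 0.31% | 99.2% |
| 0.5 | 0.62% | 91.0% |
| 0.25 | 1.24% | 70.1% |
| 0.1 | 3.10% | 38.3% |

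Under-reporting weakens any statement drawn from an absence of reports. At the higher assumed values of s, at least one event would still very probably surface.

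**5. Withdrawn children.** The article gives no expected rate of consent withdrawal. The 20% allowance is for dropout in general, so the number of children whose data would be left out cannot be calculated.

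**The case against.** The strongest reply is that this is a wording slip with little behind it. The disputed clause sits in a sentence that already calls the study minimal risk, and providing for adverse events does not contradict it, because standard care, including vaccination, carries risks of its own. Both points are fair. The conflict is with Interventions, Improving adherence and Informed consent, not with the existence of a reporting route.

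Four stronger readings are tempting, and the article does not support them.

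- *Harms would be missed.* Staff invite questions about the bracelet at each follow-up visit, mothers are later asked what they disliked, non-attenders may be contacted, and serious events have their own route.
- *Low literacy blocks reporting.* The site description says "The study introduces an intervention designed primarily for illiterate mothers", but staff may complete the form, so a mother can simply tell them.
- *Withdrawn children vanish.* The reason for withdrawal is documented and the data are retained. The exclusion applies to the final analysis, and nothing removes an incident report already filed.
- *Zero reports will be presented as proof of safety.* Safety is neither an objective nor an outcome, and the remark about baby safety is background description.

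It is also fair that a condensed article may leave form items and adverse-event tables to a fuller protocol, so a missing checklist is not by itself a fault. What remains is the untenable absolute statement, together with an event-triggered route and an exclusion rule that are stated in the text. Invited questions and a general query about dislikes may surface problems, but the article does not say that they yield a recorded count for every child given a bracelet.

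**Conclusion.** The claim that harm beyond standard care is impossible is wrong as written and should be replaced. As described, bracelet-related problems could be under-ascertained. The article does not support saying that they would be missed.

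The size of the shortfall is unknown. Complete capture with no events among 964 infants leaves a true rate of up to about 0.31% open, assuming all 964 receive the bracelet and are observed. Anything above that depends on an assumed reporting share. Coverage and timeliness conclusions do not depend on this point, and neither does the minimal-risk label on which the Data monitoring section relies. The matter deserves more than a wording edit only because better capture is available at contacts that will take place anyway.

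**What to change.** 1. In Ethics, replace the absolute clause with a statement of minimal expected risk that names the bracelet as the added exposure, consistent with Informed consent and Participant withdrawal.
2. Unless the full protocol or study forms already do so, add one recorded question on bracelet problems (for example skin injury, tightness, breakage, mouthing) to the existing follow-up visit form and to the end-of-study interview. The interview is needed because children who stop attending are not seen at visits.
3. Report descriptive counts by bracelet arm, with every child given a bracelet in the denominator. Include those later withdrawn, with the withdrawal reason that is already documented. Alongside a zero count, give the number of children actually asked and the upper bound.

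The cost is a slightly longer form and one descriptive table, with no extra visits or staff. Under the Protocol modifications section the change would go to both review boards. Because recruitment has closed, the question can be applied only to the contacts that remain, and the report should say so.
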